### Safety assessment

All enrolled patients were included in the safety assessment. Safety outcomes encompassed predefined adverse events (including ear skin rash, dizziness, palpitation, and intolerable diarrhea requiring intervention) during treatment and follow-up phases. All safety-related data were meticulously documented for safety findings.

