### Sample size

The sample size was calculated using a two-sample proportion test, with the following parameters: a two-sided significance level (*α*) of 0.05, a statistical power of 90% (*β* = 0.1), an expected qualified preparation rate of 70% for the sham TEAS group, and 85% for the active TEAS group. The calculated minimum evaluable sample size was 161 per group. Accounting for a 20% dropout rate, a total of 404 subjects were planned, with 202 subjects allocated to each group.

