#### Secondary outcomes

Defecation parameters

Following TEAS/sham-TEAS interventions, patients documented their defecation parameters in the record sheets, including first defecation time, total defecation frequency, and final stool consistency.

Colonoscope outcomes

The evaluated parameters encompassed four key indicators: insertion time, withdrawal time, cecal intubation rate (CIR), and adenoma detection rate (ADR). The insertion phase was defined as commencing with initial rectal visualization and concluding when the endoscope tip traversed the ileocecal valve into the cecal caput. Withdrawal time represents the duration from cecum to anal canal during meticulous mucosal inspection in screening or diagnostic procedures without therapeutic interventions, with a minimum 6-min benchmark indicating thorough pathological evaluation. CIR, which reflects procedural completeness through comprehensive cecal visualization including anatomical landmarks, must be maintained at ≥95% to ensure examination adequacy. ADR calculated as the percentage of colonoscopies with at least one adenoma identified.

Adverse reaction

Research staff documented all adverse reactions occurring during the bowel preparation process and post-colonoscopy, including nausea, vomiting, abdominal pain, distension, headache, and dizziness (refer to Appendix). The incidence rate of adverse reactions was calculated as (number of cases with adverse reactions)/(total number of cases).

Satisfaction and follow-up colonoscopy

At the conclusion of the treatment period, all participants were surveyed regarding their satisfaction with bowel preparation and their willingness to have a follow-up colonoscopy. The details are presented in Appendix.

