### Statistical analysis

All statistical analyses were performed using SPSS 29.0 and GraphPad Prism 10.4, adhering to the intention-to-treat (ITT) principle. Continuous variables were tested for normality using the Shapiro–Wilk test; normally distributed data were expressed as mean ± standard deviation, and non-normally distributed data as median [interquartile range]. Categorical variables were presented as frequencies and percentages. For the primary outcome (rate of adequate bowel preparation), a multivariable logistic regression model was employed to adjust for baseline covariates. Missing data were handled using Multiple Imputation by Chained Equations (MICE); 20 imputed datasets were generated, and the imputation model included all baseline variables, the grouping variable, and the primary outcome measure. To control the type I error rate for multiple secondary outcomes, a hierarchical strategy was adopted. The primary outcome was tested at *α* = 0.05. Among secondary outcomes, colonoscopy indicators were designated as key secondary endpoints and were corrected using the Holm-Bonferroni method. For these endpoints, insertion and withdrawal times (continuous variables) were compared using independent *t*-tests or Mann–Whitney *U* tests as appropriate, and cecal intubation and adenoma detection rates (categorical variables) were compared using Chi-square or Fisher’s exact tests. The remaining secondary outcomes, including bowel movement parameters, patient satisfaction scores, and adverse reactions, were treated as exploratory analyses; no multiplicity correction was applied, and *p*-values are presented for descriptive reference only. Safety profiles were described by comparing the incidence and severity of adverse events (Chi-square test) and patient satisfaction (Wilcoxon rank-sum test). Protocol deviations were addressed by per-protocol sensitivity analyses to verify the robustness of the results. A two-sided *p* < 0.05 was considered statistically significant.

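### The safety population is set by enrolment rather than exposure, so adverse-reaction rates would be diluted if any allocated patient goes untreated

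*Protocol article*

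**What the plan says.** Four places in the protocol article bear on the safety denominator.

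- **Safety assessment:** "All enrolled patients were included in the safety assessment". No exposure condition is attached.
- **Secondary outcomes (Adverse reaction):** "The incidence rate of adverse reactions was calculated as (number of cases with adverse reactions)/(total number of cases". The total is not defined.
- **Statistical analysis:** all analyses are described as "adhering to the intention-to-treat (ITT) principle", with no separate safety set. The arms are to be compared: "Safety profiles were described by comparing the incidence and severity of adverse events (Chi-square test". Adverse reactions are among the exploratory outcomes, with p-values for description only.
- **Sample size:** "Accounting for a 20% dropout rate, a total of 404 subjects were planned". The timing of that dropout relative to treatment is not given.

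Table 1 (Trial design) places screening and consent 24 h before allocation, allocation at time 0, and the intervention in the 1 h column. Enrolment, allocation and first exposure are therefore three separate moments.

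**The concern.** A patient who never takes PEG and never receives stimulation cannot react to either. If that patient stays in the denominator as a non-case, the rate is pulled down. Intention-to-treat is a sound default for the primary outcome. For tolerability the same denominator errs towards making the treatment look better tolerated. Applied to safety, it would also count a patient who received the other arm's electrode placement by mistake under the arm not received.

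Tolerability is part of what this trial sets out to show. The Introduction hypothesises that transcutaneous electrical acupoint stimulation (TEAS) eases preparation-related symptoms, and the Discussion aims to establish it as safe. The published adverse-reaction rates will be the evidence for that. The article also states its choice of safety population outright, so this is not simply a detail left to a fuller document.

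**Working it through.** **1. The plan's own figure.** The article states no expected adverse-reaction rate and no safety-set size. The related figure is the sample size, with inputs from the Sample size section: 70% vs 85%, two-sided alpha 0.05, power 90%, dropout 20%.

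n = [z(α/2)·√(2·p̄·q̄) + z(β)·√(p₁q₁ + p₂q₂)]² / (p₁ − p₂)², with p̄ = 0.775

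= [1.960 × 0.5906 + 1.2816 × 0.5809]² / 0.15² = 1.902² / 0.0225 = 160.8, so 161 per group.

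161 / (1 − 0.20) = 201.25, so 202 per group and 404 in total. The plan's figures reproduce and are not affected by this point. The 20% allowance corresponds to 202 × 0.20 = 40.4, about 40 patients per arm.

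**2. Dilution within an arm.** Let π be the true rate among exposed patients and u the share of allocated patients who are never exposed and are counted without an event. Then

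reported rate = π × (1 − u).

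The article does not give u. For π, 37% is the gastrointestinal intolerance rate that the Discussion cites from a PEG trial. It is used here only as an assumption, beside 20% and 10%.

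| u | Unexposed per arm (202u) | π = 37% | π = 20% | π = 10% |
|---|---|---|---|---|
| 0% | 0 | 37.0% | 20.0% | 10.0% |
| 2% | 4.0 | 36.3% | 19.6% | 9.8% |
| 5% | 10.1 | 35.2% | 19.0% | 9.5% |
| 10% | 20.2 | 33.3% | 18.0% | 9.0% |
| 20% | 40.4 | 29.6% | 16.0% | 8.0% |

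The last row requires every planned dropout to occur after allocation but before any exposure.

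**3. Comparison between arms.**

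- *Equal u:* (1 − u) cancels from the risk ratio, and the absolute difference shrinks by (1 − u). With an assumed 37% vs 25%, the difference of 12.0 points becomes 12.0 × 0.95 = 11.4 at u = 5% and 12.0 × 0.80 = 9.6 at u = 20%.
- *Unequal u, no true effect:* the apparent risk ratio is (1 − u₂)/(1 − u₁). For 0% and 5% unexposed it is 0.95/1.00 = 0.95.

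**4. Who can enter an arm-level rate.** By Table 1, a patient lost between enrolment and allocation has no arm. Such a patient could dilute only a rate pooled over the whole trial. For the arm-level rates, u concerns patients lost between allocation and first exposure.

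**The case against.** The strongest reply is that the article never says any patient is unexposed, or that an unexposed patient would be scored as event-free.

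- **The 20% allowance has no stated timing.** It is added to a minimum evaluable number for the bowel-preparation endpoint. It may largely cover patients who were fully treated but had no assessable colonoscopy, and they belong in any safety set.
- **The handling of missing safety data is not stated.** The article says "Missing data were handled using Multiple Imputation by Chained Equations (MICE" without saying whether this covers adverse reactions. If unexposed patients were treated as missing and left out, there would be no dilution.
- **Enrolled may mean treated.** The Bowel preparation section describes enrolled subjects as those who took the PEG, and inclusion in the safety assessment may mean only that everyone is monitored.
- **The setting makes u small.** Recruitment is limited to supervised inpatients, and treatment is one 1-h session starting with the first PEG intake.
- **Safety is exploratory**, and separate wards, operator certification and record audits make wrong-arm delivery unlikely.

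Most of this stands as to size. It does not remove the point. The Bowel preparation text describes the planned regimen and does not define enrolment, which Table 1 puts before allocation. The listed imputation model names baseline variables, group and the primary outcome, not adverse reactions, and imputing reactions to a treatment never received would make little sense. Exploratory status governs the p-values, not the correctness of a published rate.

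A reader might also infer a spurious difference between arms, for example 29.6% vs 33.3% (3.7 points) from 20% unexposed in one arm and 10% in the other at π = 37%. The documents do not support that split. Patients are blinded and the sham uses the same device and parameters, so there is no evident reason for arm-related loss before exposure. With 202 per arm, the standard error of a difference between rates near 31% is √(2 × 0.31 × 0.69 / 202) = 4.6 points, so even that scenario is under one standard error.

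**Conclusion.** The point holds conditionally and is minor. The safety population is defined by enrolment, the rate has an undefined total as its denominator, and no other section adds an exposure condition. Under that rule, rates are understated by a relative amount u if unexposed patients exist and are counted without an event. The range runs from no effect at u = 0 to one fifth at u = 20%, and the setting points to the low end.

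A reader might conclude that the trial's adverse-reaction rates are in fact understated, or that the planned 20% are untreated patients. The documents support neither. They give no u, no timing of dropout and no scoring rule for unexposed patients. The 37% is borrowed from a cited study as an illustration. The sample size and the primary conclusion are unaffected.

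**What to change.** Replace the sentence in Safety assessment with: *The safety set is all randomised patients who took any PEG or received any stimulation (TEAS or sham), analysed by the stimulation actually received.* Name this set as the denominator of the adverse-reaction rate under Secondary outcomes, and report by arm how many patients were randomised but not exposed.

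One set is enough, because stimulation starts with the first PEG intake and the listed reactions are not attributed to PEG or device. A patient who took PEG but received neither form of stimulation cannot be classified by stimulation received. State how such a patient is counted, for instance under the randomised arm and listed separately.

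The cost is wording in two sections and one extra line in the participant flow. No new data are needed, since stimulation settings and compliance are already recorded (Data collection and management). The downside is that reported adverse-reaction rates may be slightly higher.

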#### TEAS and sham-TEAS

TEAS Protocol: The TEAS intervention protocol employed an acupoint combination targeting *Neiguan* (PC6) and *Zusanli* (ST36) (see Figure 2 for anatomical landmarks). PC6 acupoint is located on the anterior forearm, 2 cun proximal to the transverse wrist crease, between the tendons of the palmaris longus and flexor carpi radialis muscles. ST36 acupoint is situated on the anterolateral aspect of the leg, 3 cun inferior to the lower border of the patella, one finger-breadth lateral to the anterior crest of the tibia. Pre-intervention anatomical validation by acupuncturists (<3 mm positioning tolerance). The stimulation system comprised hydrogel self-adhesive electrodes (diameter: 20 mm) interfaced with a transcutaneous acupoint electrical stimulator (SNM-FDCM01, Ningbo Maida Medical Instrument Company, Ningbo, China). The intervention period overlapped with the PEG administration period and lasted 1 h from the first dose of PEG ingestion (Figure 3). The stimulation parameters were set as follows: a train on-time of 2 s and off-time of 3 s, pulse width of 0.5 ms, pulse frequency of 25 Hz, and amplitude of 2–10 mA (at the maximum level tolerated by the subject).

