**Figure 3 fig3:**
[figure not shown]
The administration of TEAS treatment protocol.

Sham-TEAS Protocol: Sham acupoint stimulation was performed using the same devices to provide identical parameters as TEAS, with sham points positioned outside the anatomical course of relevant meridians: the sham-point of PC6 is approximately 15 cm up to the elbow joint and lateral to the real PC6 acupoint and the sham-point of ST36 is approximately 10 cm down to the knee and lateral to the real ST36 acupoint. The temporal schedule and ancillary procedures (electrode placement duration, PEG coordination) mirrored the intervention group.

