### Adverse reaction

Adverse reaction associated with bowel preparation and colonoscopy procedures—including nausea, vomiting, abdominal pain, bloating, headache, and dizziness—were prospectively categorized by blinded independent assessors.

1) Transient symptoms requiring no intervention, with preserved procedure tolerability;
2) Symptom-driven procedural pauses (<5 min) without compromising examination completion;
3) Intolerable symptoms necessitating premature procedure termination;

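### The only predefined skin event is at the ear, where no electrode is placed; no list names reactions at the forearm and leg electrode sites, and the two event lists share only dizziness

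*Protocol article*

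**What the plan says.** **Safety events.** The Safety assessment section includes everyone enrolled and covers "predefined adverse events (including ear skin rash, dizziness, palpitation, and intolerable diarrhea requiring intervention". It adds that safety data were thoroughly documented.

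**Electrode sites.** Under TEAS and sham-TEAS, "PC6 acupoint is located on the anterior forearm" and "ST36 acupoint is situated on the anterolateral aspect of the leg". In the sham arm, "the sham-point of PC6 is approximately 15 cm up to the elbow joint" and "the sham-point of ST36 is approximately 10 cm down to the knee", each also moved laterally. Device and settings are the same in both arms.

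**Adverse reactions.** Under Secondary outcomes: "Research staff documented all adverse reactions occurring during the bowel preparation process and post-colonoscopy, including nausea, vomiting, abdominal pain, distension, headache, and dizziness". Incidence is cases with a reaction divided by all cases. The Appendix repeats the same six symptoms (bloating in place of distension) and gives its scope as "Adverse reaction associated with bowel preparation and colonoscopy procedures". It grades them in three levels, according to whether the procedure was tolerated, briefly paused or ended early.

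**Analysis.** The Statistical analysis section compares the incidence and severity of adverse events by chi-square test. It treats adverse reactions as exploratory, with descriptive p-values.

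**The concern.** An ear rash would be a natural local event for a device worn on the ear. Here it does not correspond to any electrode, active or sham. Because it is the only skin item in any list, the plan has no named event for the harm most specific to a skin-electrode device.

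The article knows that this harm is possible. The exclusion criteria remove patients allergic to the electrodes or to skin preparation, and the rationale for the stimulation parameters says that individual intensity setting avoids pain and injury to the skin. The Discussion states the aim of establishing the stimulation as safe. A claim of that kind needs an event that could contradict it, asked about in the same way in both arms.

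A second difficulty is that two differing event lists feed one planned comparison of adverse events, and the text does not say which events count.

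**Working it through.** The plan gives no figure on this point, so the check sets the sections side by side.

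**Step 1: does any electrode site match the ear item?**

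| Electrode | Site | Source |
|---|---|---|
| Active, PC6 | anterior forearm | TEAS and sham-TEAS |
| Active, ST36 | anterolateral leg | TEAS and sham-TEAS |
| Sham for PC6 | towards the elbow, lateral | Sham-TEAS Protocol |
| Sham for ST36 | below the knee, lateral | Sham-TEAS Protocol |

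None is on the ear, and nothing else in the article is applied there.

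**Step 2: compare the named events.**

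| Event | Safety assessment | Secondary outcomes and Appendix |
|---|---|---|
| Ear skin rash | yes | no |
| Palpitation | yes | no |
| Intolerable diarrhoea | yes | no |
| Dizziness | yes | yes |
| Nausea | no | yes |
| Vomiting | no | yes |
| Abdominal pain | no | yes |
| Distension or bloating | no | yes |
| Headache | no | yes |
| Skin reaction or pain at an electrode site | no | no |

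Named events: 4 in the first list and 6 in the second, with 1 shared. Distinct events = 6 + 4 − 1 = 9, or 8 without the ear item. Three are only in the safety list and five only in the adverse-reaction list. The last row is in neither and is not part of the 9.

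**Step 3: do the severity grades fit an electrode-site reaction?** Stimulation lasts 1 h from the first PEG intake, and PEG is taken 4 to 6 h before endoscopy. If that window is counted from the first intake, stimulation ends 4 − 1 = 3 h to 6 − 1 = 5 h before the colonoscopy. A skin reaction at the forearm or leg would rarely pause or end the examination. The lowest grade could be stretched to cover a brief, untreated reaction. A reaction that lasts or needs treatment, without disturbing the procedure, has no grade.

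**Step 4: what enters the comparison?** A patient whose only event is palpitation is a named case in the safety list but not in the adverse-reaction list. A patient whose only event is nausea is the reverse. The Statistical analysis section refers to adverse events without saying which list, or whether both, define a case.

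**Step 5: is the sample size affected?** No. The stated 161 per group reproduces from 70% against 85% at two-sided alpha 0.05 and 90% power (pooled variance, no continuity correction). Then 161 / 0.80 = 201.25, rounded up to 202 per group and 404 in total. No safety event enters that calculation.

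**The case against.** The strongest reply is that both lists are open. Each is introduced as a set of examples, research staff record every adverse reaction from bowel preparation onwards, and the stimulation hour lies inside that window. A reaction under a forearm or leg electrode is therefore recordable as the plan stands. This is right. A reader might infer that local device harm is not captured at all, or that its recorded rate is about 0% by construction. The first is contradicted by the open wording. The second is true only of the literal ear item and says nothing about reactions elsewhere.

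It can also be said that the lists differ in scope, one for symptoms of preparation and colonoscopy and one for general safety, and that a single incidence formula applies to all reactions. This too has weight: two conflicting incidences are not established. But scope does not separate the lists cleanly. Intolerable diarrhoea, plainly related to preparation, is only in the general list, and dizziness is in both. The composition of the comparison remains unclear.

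Finally, these outcomes are exploratory, and an article may leave the full event checklist to the complete protocol. That lowers the severity, but it does not explain a specific item that the article states at the wrong site.

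**Conclusion.** The point holds as a wrong item and an unreconciled list in an operative safety section. The ear rash matches none of the four electrode positions. No named item covers the sites in use. The two lists share 1 of 9 named events. The consequence is that capture of local reactions depends on unprompted recording, without a severity grade that suits them, and that the case definition for the adverse-event comparison is unclear.

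Up to 404 patients are exposed to skin electrodes for 1 h, since both arms use the same device and settings. The number actually stimulated may be lower, given the 20% dropout allowed for. How many local reactions would go unrecorded cannot be estimated from the article.

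Severity is moderate. The primary outcome, sample size, alpha and power do not change. What is weakened is the support for a statement that the stimulation is safe. The conclusion assumes that the article's event lists reflect what the case report form prompts for. If the form already carries an electrode-site item, only the text needs correcting.

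**What to change.** 1. In Safety assessment, replace the ear item with: *skin reaction or pain at any electrode site (forearm and lower leg, real or sham point)*. Record it in the same way in both arms when the electrodes are removed.
2. Reconcile Safety assessment, the adverse-reaction paragraph under Secondary outcomes, and the Appendix into one event list. State that this list, together with any unlisted event recorded, defines a case for the incidence and for the chi-square comparison. Report each event by arm.
3. State how severity is recorded for electrode-site reactions, since the Appendix grades rest on the course of the procedure.
4. Keep the safety population as stated in Safety assessment.

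The cost is one line on the case report form and some protocol wording. No extra visit is needed, and the sample size does not change.

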## Discussion

This study proposes a novel therapeutic paradigm integrating traditional meridian theory with contemporary neurogastroenterology, hypothesizing that TEAS at gastrointestinal-associated acupoints (ST36 and PC6) may optimize bowel preparation efficacy while mitigating laxative-related discomfort. To our knowledge, this randomized controlled trial represents the first clinical investigation employing TEAS as an adjunctive modality for bowel preparation in colonoscopy, constituting an original contribution to endoscopic preparation research.

Despite established protocols, suboptimal bowel preparation remains a persistent challenge in gastrointestinal endoscopy, with multicenter studies revealing inadequate cleansing rates ranging from 20 to 40% across diverse populations (13, 14, 46, 47). The predominant use of PEG solutions, while effective, is marred by significant limitations: a multicentre randomized controlled trial (*n* = 422) documented 37% gastrointestinal intolerance rates, including nausea, bloating, abdominal pain/cramps and anal irritation, contributing to 17.8% patient refusal to-repeat the same preparation for subsequent colonoscopies (48). More critically, the ability to detect adenomas and advanced adenomas is significantly hampered by inadequate bowel preparation. A systematic review and meta-analysis of 11 studies (more than 55,000 colonoscopies) identified inadequate preparation as the primary contributor of missed neoplastic lesions, with ADR decreasing by 5% in poorly prepared segments (49). Yang et al. (50) revealed that 15–37% of screening candidates experience anxiety regarding bowel preparation regimens, which consequently compromises strict adherence to prescribed purgative protocols and dietary restrictions. In conclusion, such preparation failures impose substantial clinical and economic burdens while posing risks and inconveniences for patients (51). Therefore, high-quality bowel preparation serves as an indispensable prerequisite for enhancing ADR and decreasing procedure-related complication rates, while ensuring screening efficacy and patient safety.

In order to solve these problems, several bowel preparation agents, including sodium picosulfate-magnesium citrate, ascorbate-enriched PEG, sodium phosphate solution, and oral sulfate solution, were developed; however, with the exception of oral sulfate solution, none achieved the 90% quality benchmark (52). In addition, these hyperosmotic and stimulant agents have been reported to increase risks such as colonic ischemia, renal impairment, and electrolyte disturbance (11). A clinical study involving 271 elderly constipated patients demonstrated that abdominal vibration (physical stimulation) combined with walking exercise achieved an adequate bowel preparation rate of 92.2% (53). For outpatients, interval walking exercise implemented after PEG administration prior to colonoscopy also proved effective in improving bowel preparation quality (54). The limitation lies in the population-specific efficacy of this intervention, showing more pronounced effects in elderly patients and young, non-obese, ambulatory patients without a history of abdominal or gynecological surgery (53, 54). Dietary interventions including clear liquid diets and low-residue diets (LRD), are also widely adopted for bowel preparation (55, 56); however, notable limitations such as the time-consuming, patient discomfort, and lack of convenience hinder the application of these methods (14). Some authors even argue that LRD may reduce bowel motility and prolong intestinal transit, resulting in effects contrary to the intended purpose, particularly in constipated patients (57). In summary, it is necessary to explore an adjuvant regimen for bowel preparation characterized by broad applicability across populations, favorable safety profile, high patient compliance, and superior cost-effectiveness.

Acupuncture is a nonpharmaceutical technique that originated in China and has been used for over 3,000 years. TEAS is a modification of traditional acupuncture (58–60), which combines the advantages of acupuncture and percutaneous electrical nerve stimulation. Unlike traditional acupuncture requiring skin penetration, this transcutaneous approach exhibits notable application prospects via its non-invasive nature, user-friendly operation, and portability (27, 61–63), while concurrently reducing infection risks and improving patient compliance (64). In recent years, a growing number of investigations have put a spotlight on the therapeutic effects of TEAS in intestinal dysmotility disorders. Clinical trials demonstrated that ST36 acupoint stimulation effectively enhances spontaneous bowel movements, alleviates constipation symptoms, and improves quality of life (65), while PC6 application demonstrates marked efficacy in reducing postoperative nausea and vomiting incidence within 24 h (66). While transabdominal or abdominal surface stimulation is theoretically more direct, limb acupoint TEAS is a superior adjunctive choice based on current evidence and operational feasibility. This study implemented a standardized stimulation parameter protocol (0.5-ms pulse width, 25 Hz frequency, and 2–10 mA amplitude) (42, 43, 67), developed based on prior clinical trial evidence to ensure intervention stability and experimental reproducibility. This study recruited only inpatients, which may limit the generalizability of our findings to the broader outpatient colonoscopy population. The inpatient setting was chosen to ensure protocol adherence and intervention fidelity, but future multicenter, pragmatic trials in outpatient settings are needed to validate the real-world applicability of TEAS as an adjunct to bowel preparation. Additionally, although we standardized endoscopist experience and withdrawal time, ADR remains influenced by multiple operator-dependent factors, and residual confounding cannot be fully excluded.

This protocol employs validated stimulation parameters (25 Hz frequency, 60-min sessions) combined with standardized laxative regimens, aiming to establish TEAS as a safe strategy for enhacing bowel preparation and alleviating adverse effects (e.g., bloating and nausea).

